## Abstract

**Background:**

Androgen deprivation therapy (ADT) is a cornerstone in the treatment of advanced prostate cancer. Adverse musculoskeletal and cardiovascular effects of ADT are widely reported and investigations into the potential of exercise to ameliorate the effects of treatment are warranted. The ‘Football Club (FC) Prostate’ study is a randomized trial comparing the effects of soccer training with standard treatment approaches on body composition, cardiovascular function, physical function parameters, glucose tolerance, bone health, and patient-reported outcomes in men undergoing ADT for prostate cancer.

**Methods/Design:**

Using a single-center randomized controlled design, 80 men with histologically confirmed locally advanced or disseminated prostate cancer undergoing ADT for 6 months or more at The Copenhagen University Hospital will be enrolled on this trial. After baseline assessments eligible participants will be randomly assigned to a soccer training group or a control group receiving usual care. The soccer intervention will consist of 12 weeks of training 2–3 times/week for 45–60 min after which the assessment protocol will be repeated. Soccer training will then continue bi-weekly for an additional 20 weeks at the end of which all measures will be repeated to allow for additional analyses of long-term effects. The primary endpoint is changes in lean body mass from baseline to 12 weeks assessed by dual X-ray absorptiometry scan. Secondary endpoints include changes of cardiovascular, metabolic, and physical function parameters, as well as markers of bone metabolism and patient-reported outcomes.

**Discussion:**

The FC Prostate trial will assess the safety and efficacy of a novel soccer-training approach to cancer rehabilitation on a number of clinically important health outcomes in men with advanced prostate cancer during ADT. The results may pave the way for innovative, community-based interventions in the approach to treating prostate cancer.

**Trial registration:**

ClinicalTrials.gov: NCT01711892

## Background

Prostate Cancer (PCa) is the most common non-cutaneous malignancy in men, with 650,000 estimated new cases per year in the developed world [1]. Androgen deprivation therapy (ADT) remains a cornerstone of PCa management, with approximately 50% of men diagnosed with PCa undergoing ADT at some point in time [2]. ADT is administered with curative intent before and 2–3 years after radiotherapy for locally advanced disease [3], or as continuous palliative treatment for disseminated disease [4]. The 15 year relative survival rate now exceeds 90% for all PCa stages combined and there has been a steady increase in the number of PCa survivors [5], partly attributable to the greater anti-neoplastic efficacy of ADT and radiotherapy in combination.

While ADT contributes to improved life expectancy, it is also associated with significant adverse effects, including loss of lean body mass (LBM), decreased bone mineral density (BMD), poor functional performance, increased fat percentage, insulin resistance, and increased risk of fractures [6-10]. The combination of ADT-induced adverse effects and subsequent changes in health behavior, i.e., physical inactivity and deconditioning, may predispose PCa patients to serious morbidity, including elevated risk of cardiovascular and metabolic disorders, leading to increased mortality [11,12]. Therefore, interventions aimed at counteracting ADT-induced adverse effects may result in profound survival benefits for patients with PCa.

Physical exercise is emerging as a promising supplementary treatment strategy in the oncology setting, with capacity to improve aerobic fitness, muscle strength, body composition, quality of life (QoL) and physical function, and to reduce fatigue [13,14]*.* Indeed, such improvements have been reported after physical exercise in studies of PCa patients undergoing ADT. Galvão et al. found that 12 weeks of combined resistance and aerobic training improved muscle mass, muscular strength, physical function and balance [15]. In agreement with these results, Segal et al. [16] found that a 24 week program of aerobic exercise combined with resistance training mitigated fatigue and maintained aerobic fitness in PCa patients undergoing radiotherapy with or without concurrent ADT. Although data from these and other randomized controlled trials (RCTs) [17-19] suggest that physical exercise interventions have considerable potential in counteracting treatment-related side-effects, important questions remain unanswered. First, the duration of interventions to date has been relatively brief (i.e., 12 or 24 weeks), and consequently little is known about whether effects of training can be maintained or even improved in the longer term. Secondly, the effects of exercise on numerous physiologic outcomes, i.e., bone metabolism, glucose tolerance, cardiac structure and function and peripheral vascular function, have yet to be described in PCa patients. Thirdly, information about the safety, feasibility and efficacy of exercise interventions for PCa patients with advanced stage disease involving bone metastases is scarce, as only one previous study has included this population [19]. Finally it is not known whether results demonstrated in previous exercise studies can be reproduced in alternative and non-clinical settings, e.g., organized team sports [14].

Therefore the purpose of the present study is to investigate 1) the effects of 12 weeks of recreational soccer on body composition, fitness, cardiac structure and function, peripheral vascular function, blood pressure, physical function parameters, postural balance, muscle strength, glucose tolerance, insulin sensitivity, and markers of inflammation and bone metabolism and 2) whether potential physiological and patient-reported effects of the 12 week soccer training intervention can be maintained or improved further with an additional 20 weeks training at a reduced training volume. The primary study endpoint is changes in LBM from baseline to 12 weeks.

## Methods/Design

### Study design

This study is a two-armed RCT, with one group playing soccer (intervention group) and a waiting-list control group, who is offered participation in the intervention after the 8 months study period. The study has been approved by the Danish National Committee on Biomedical Research Ethics for the Capital Region (registration number H-3-2011-131) and written informed consent will be obtained from all participants before any study procedures are undertaken.

### Blinding and masking of data

Blinding of patients and soccer instructors in this kind of study is not possible. All data will be entered into a secure web server immediately after collection and will not be available to study personnel at subsequent tests. At the termination of the study a statistician blinded to treatment assignment will perform all analyses before disclosing any study outcome data to the study coordinator and researchers involved in the study.

### Study population

We aim to include and randomize 80 men with histologically confirmed advanced or locally advanced PCa presenting at Copenhagen Prostate Cancer Center and Dept. of Urology, Copenhagen University Hospital Rigshospitalet, Denmark. Patients aged < 76 years who have received ADT for at least 6 months will be invited to attend meetings which will outline the purpose of the study, and offer more detailed information about the investigations involved and the soccer intervention.

Assessments will be performed at the following locations: The Panum Institute Copenhagen (dual-energy X-ray absorptiometry [DXA] scans), The August Krogh Building at the Department of Nutrition, Exercise and Sports (cardio respiratory fitness test, peripheral vascular function tests, electrocardiogram), The National Research Centre for the Working Environment (balance, jump, chair stand and stair climbing tests) and Department of Cardiology, Copenhagen University Hospital, Gentofte Hospital, Denmark (echocardiography). All training sessions will take place at The Department of Nutrition, Exercise and Sports, University of Copenhagen.

### Inclusion criteria

•Patients with locally advanced or advanced PCa managed with medical or surgical ADT for at least 6 months.

•Age between 18 and 76 years.

•Ability to read and understand Danish.

•Signed informed consent.

### Exclusion criteria

•WHO performance level > 1.

•Osteoporosis (T-score < −2.5).

•Activity limiting pain from bone metastasis.

•Cardiovascular or pulmonary disorders (e.g., arrhythmias, ischemic heart disease, unregulated high blood pressure, chronic obstructive lung disease).

•Anticoagulant therapy.

•Abnormal screening blood samples (hemoglobin <7.0 mM, creatinine >150 mikroM, thrombocytes <150,000/mikroL).

•Abnormal liver function.

•Coagulopathy.

•Malignant disease other than PCa.

•Current or scheduled chemotherapy.

### Randomization

After successful completion of all baseline assessments participants are randomized 1:1 to the soccer intervention or control group. The randomization process will be conducted by a research consultant at The Copenhagen Trial Unit who has no other involvement in the study. The study flowchart is presented in Figure 1.

**Figure 1 F1:**
[figure not shown]
CONSORT diagram.

### Treatment arms

#### Intervention group

Participants in the intervention group will practice soccer for 12 weeks two-three times weekly. An experienced soccer instructor will be in charge of all training sessions. During weeks 1–4 training will consist of two weekly sessions of 15 min of warm-up exercises (running, dribbling, passing, shooting, balance and muscle strength exercises) followed by 2 × 15 min of 5–7 a-side games. In weeks 5–8 the duration of each session will increase to 3 × 15-min games after the warm-up, and in weeks 9–12 there will be three weekly training sessions of the same duration. After 12 weeks all assessments will be repeated. Participants in the intervention group will then continue bi-weekly supervised training for an additional 20 weeks at the end of which all assessments will be repeated to allow for additional analysis of long-term effects (Figure 2). Training will take place on a natural grass pitch. In adverse weather conditions (i.e., < 5°C or heavy rain) training will be performed indoors. Participants will be told to avoid hard tackles and other actions that carry a risk of injury.

**Figure 2 F2:**
[figure not shown]
Duration and frequency of soccer training sessions during the study period.

#### Control group

Participants in the control group will be encouraged to maintain their baseline physical activity level. However, for ethical reasons, this advice will not be enforced, since increasing physical activity levels in general is considered beneficial to health.

### Study assessments

All assessments will take place at baseline, and after 12 weeks and 32 weeks. Measurement of body composition, peripheral vascular function, glucose tolerance, blood pressure, and blood markers will be performed in the morning after an overnight fast. Subjects will be instructed to avoid intake of medication, caffeine and vitamins, and to abstain from tobacco use for 12 h prior to the above mentioned tests and to avoid strenuous physical activities 48 h prior to all examinations.

#### Primary study endpoint

The primary study endpoint is the change in LBM as determined by whole body DXA-scan (iDXA, Lunar Corporation, Madison, WI, USA) according to standard procedures.

#### Secondary study endpoints

Secondary outcomes include body composition, measures of physical functioning, assessment of cardiovascular and metabolic function, blood test values and patient-reported outcomes.

### Body composition

Assessment of total body BMC and areal BMD as well as android, gynoid and total body fat mass will be derived from the whole body DXA scan. Visceral fat mass will be evaluated using the iDXA CoreScan software (Lunar Corporation, Madison, WI, USA). BMC and areal BMD of the hips and lumbar spine will be derived from separate DXA scans. Height will be measured by a stadiometer, body weight will be measured with a digital platform scale and body mass index will be calculated (weight in kg/(height in m)^2^).

### Waist- and hip circumference

Waist circumference will be measured around the abdomen at the level of the belly button, and the hip circumference will be measured at the widest part of the hips and hip to waist ratio will be calculated [20].

### Physical function tests

#### Maximal oxygen uptake

Two hours after consuming a normal breakfast participants will conduct a submaximal walking test on a treadmill and an incremental test to exhaustion on a cycle ergometer. The submaximal test will consist of 4 min of walking on a treadmill at 4.5 km/h to determine oxygen uptake, respiratory exchange ratio and heart rate during an activity similar to that of daily living. After 4 min of passive rest, the incremental cycle test will start with 4 min cycling at 40 W, with a self-chosen cadence in the range of 70–90 rpm, after which the load will increase by 20 W each min until volitional exhaustion. Oxygen uptake, respiratory exchange ratio (RER) and ventilation will be determined by pulmonary gas exchange measurements (MasterScreen CPX, Viasys Healthcare, St Paul, Minnesota, USA). The physiological criteria for approval of the maximal oxygen uptake (VO_2_max) test will be RER ≥ 1.05 and leveling off on the VO_2_ curve with an increase of <1 ml O_2_/min/kg with an increase in work load of 20 W [21]. Heart rate will be determined in 5 s intervals throughout the incremental test by a Polar Team System chest belt (Polar Oy, Kempele, Finland). VO_2_max and maximal heart rate (HRmax) will be defined as the highest oxygen uptake and heart rate values obtained over a 30 and 15 s period, respectively.

#### Flamingo balance test

Postural balance will be assessed with a modified single-leg flamingo balance test [22]. Subjects are instructed to stand on one foot on a 3 cm wide and 5 cm high metal bar with their eyes open for one min. Subjects are permitted to move their arms and non-standing leg to assist balancing. The number of falls will be counted and used as a measure of postural balance.

#### Assessment of postural sway

Subjects will be asked to stand on a force platform (AMTI R6-1000, Watertown, MA, USA), arms crossed over the chest, and instructed to look at a 10 cm^2^ circle placed 2.5 meters away from the platform at a height of 1.65 m. Vertical ground reaction force (Fz), anterior-posterior moment (Mx) and medio-lateral moment (My) will be sampled using custom made Matlab (Mathworks) acquisition software at 100 Hz (16 bit A/D conversion, DT9804, Data translation, Marlboro, MA, USA). The Fz-, Mx- and My-signals will be digitally low-pass filtered with a 4^th^ order zero-lag Butterworth filter (8 Hz cutoff) [23]. Displacement of the center of pressure will be calculated as (x,y) = (x_0_ + My/Fz, y_0_ + Mx/Fz), where (x_0,_y_0_) is the geometrical center of the plate. Balance will be tested in three positions: 1) bilateral (60 s): feet close together with skin contact both at heels and bases of hallux; 2) unilateral (15 s): base of hallux of the free foot placed on medial malleolus of the standing leg; 3) tandem stand (15 s): both feet on the force plate with base of hallux of one foot placed next to medial malleolus of the other foot. Bilateral standing is performed once, unilateral and tandem standing are performed in triplicate and the trials with the smallest sway area will be used for further analysis. The data acquisition method has been previously described in detail elsewhere [24].

#### Counter movement jump (CMJ)

On a force platform (AMTI R6-1000, Watertown, MA, USA) subjects will perform standard CMJs with hands placed on the hips. On the signal “go” the subject is instructed to bend their knees and jump as high as they can without moving their hands. The vertical force signal (Fz) obtained during the jump will be used to calculate the offset impulse, i.e., the area under the force-time curve, which will then be converted to velocity by dividing by body mass, and finally converted to jump height based on the relationship between kinetic and potential energy [25]. Subjects will perform three jumps separated by 30-s resting periods and the highest jump height (cm above ground) will be used in subsequent analysis.

#### Sit-to-stand test

Using a chair fixed to the ground with a seat 45 cm above the ground subjects will be instructed to sit in the middle of the chair, back straight, arms crossed over their chest, feet flat on the floor. A mechanical contact in the seat is connected to a computer which automatically counts the number of rises. Correct standing technique will be demonstrated first slowly, then quickly. Subjects will be allowed to practice for two-three repetitions before the start of the test. On the signal “go” the subject will be asked to stand, then return to the seated position, as many times as possible in 30 s [26].

#### Stair climbing

Subjects will be instructed to climb up one flight of a staircase (9 steps, 0.175 m each) as fast as they safely can, taking one stair at a time, without holding the handrails [27]. The time taken by the subject between touching the first step to reaching the last step will be measured manually with a stopwatch.

#### Muscle strength

Dynamic concentric muscle strength for the knee extensors will be assessed with the one repetition maximum (1RM) test measured in 2.5 kg intervals. After a standardized warm-up the test load will start at 15 kg and resistance will gradually be increased until failure. The rest period between each attempt is 30 seconds. The maximum weight lifted through a full range of motion will be recorded as 1 RM [28].

### Cardiovascular and metabolic function

#### Echocardiography

Comprehensive transthoracic echocardiography will be performed on a GE Vivid 9 ultrasound machine with a 2.5 MHz transducer (GE Healthcare, Horton, Norway). The examination will be performed with the subjects resting in lateral supine position in a dark room by two experienced echocardiographers blinded for group allocation. All examinations will be analyzed off-line in random order, using the Echo Pac software version BT 11.0 by an independent and blinded echocardiographer. The full echocardiographic protocol has been described elsewhere [29]. Cardiac structure will be evaluated from parasternal long axis 2-D recordings at the mid-ventricular level with measurement of left ventricular (LV) end-diastolic diameter (LVEDD), interventricular septal wall thickness (IVST) and posterior wall thickness (PWT). LV mass is calculated from the formula 0.832 [1.05 [(LVID + IVST + PWT)^3^] − (LVID)^3^] and indexed according to body surface area and LV volumes. LV ejection fraction will be evaluated with Simpson’s biplane method.

Right ventricular function will be evaluated as tricuspid annular plane systolic excursion. Diastolic function will be measured as peak transmitral inflow velocity in early (E) and late (A) diastole and the corresponding E/A-ratio and pulsed analyses of tissue Doppler Imaging (TDI) of diastolic velocities E´ and A´ will be obtained with a 5-mm pulsed (TDI) sample volume placed in the lateral, septal, anterior and inferior plane of the mitral annulus in the 2- and 4-chamber apical views. TDI peak systolic velocity (S´; cm/s) will also be measured. The values of E´ will be reported as an average of the septal and lateral early peak diastolic velocities and E/E´ will be calculated as a measure of left ventricular filling pressure. Two-D color tissue Doppler will be evaluated from six basal segments of septal, lateral, anterior, inferior, posterior, and anterior septal walls of the apical 2- and 4-chamber and long axis and values will be averaged. Measurements will include S´, E´ and A´. Diastolic dysfunction will be graded as previously described [29]. LV longitudinal systolic function will be evaluated by 2D- speckle tracking analysis and longitudinal 2-D global strain will be estimated using automated functional imaging. LV longitudinal systolic shortening (LV displacement) will be evaluated using tissue tracking as described previously by others [30].

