## Abbreviations

ADT: Androgen deprivation therapy; BMC: Bone mineral content; BMD: Bone mineral density; DXA: Dual-energy X-ray absorptiometry; IVST: Interventricular septal wall thickness; LBM: Lean body mass; LV: Left ventricular; LVEDD: Left ventricular end-diastolic diameter; LVID: Left ventricular internal dimension; OGTT: Oral glucose tolerance test; PAT: Peripheral arterial tonometry; PCa: Prostate Cancer; PWT: Posterior wall thickness; QoL: Quality of life; RER: Respiratory exchange ratio; RHI: Reactive hyperemic index; RM: Repetition maximum; TDI: Tissue doppler Imaging; VO2max: Maximal oxygen uptake.

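### The printed left ventricular mass formula applies 1.05 to the outer cube only, so every LV mass is slightly too high by an amount that depends on cavity size

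*Protocol article*

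**What the plan says.** The Echocardiography section of the protocol article lists three directly measured dimensions for cardiac structure: the LV end-diastolic diameter (LVEDD), "interventricular septal wall thickness (IVST) and posterior wall thickness (PWT"). It then fixes how mass is derived from a cavity diameter and the two wall thicknesses: "LV mass is calculated from the formula 0.832 [1.05 [(LVID + IVST + PWT)^3^] − (LVID)^3", with the outer bracket closing after that cube.

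The brackets balance. The inner pair encloses only the cube of the summed dimensions, and the cavity cube is subtracted outside that pair. The list of abbreviations gives "LVID: Left ventricular internal dimension", so LVID is the cavity. The result is then "indexed according to body surface area and LV volumes". The formula appears nowhere else in the article. For the full echocardiographic protocol the section refers to a cited source, and it names the off-line analysis software.

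**The concern.** LVID is the inside of the ventricle, and LVID + IVST + PWT is the outside. The cube of the outside minus the cube of the inside is therefore the wall, and wall mass should be a constant times that difference. In the printed rule one of the two constants reaches only the first cube. The subtraction no longer isolates the wall, and 5% of the outer cube's counterpart in the cavity is left in the result.

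Anyone who derived LV mass from this text would obtain values that are too high. The excess varies with cavity size, so it would not be a fixed offset across participants, nor within a participant whose cavity changes. Cardiac structure is among the study aims in the Background, and LV mass and its index are the derived measures of structure.

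**Working it through.** **Inputs from the document.** The constants 0.832 and 1.05, the placement of the brackets, and LVID as internal dimension. The article states no LV mass value, so there is no printed result to reproduce.

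**Assumptions.** The article gives no numeric dimensions. I take LVID 4.0–6.0 cm and IVST = PWT = 0.8–1.2 cm, with results read in grams.

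**Notation.** L = LVID and D = LVID + IVST + PWT.

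- As printed: M1 = 0.832 × (1.05 × D^3 − L^3)
- With 1.05 on the whole difference: M2 = 0.832 × 1.05 × (D^3 − L^3) = 0.8736 × (D^3 − L^3)
- Excess: M1 − M2 = 0.832 × 0.05 × L^3 = 0.0416 × L^3

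The excess is above 0 for every L above 0 and does not contain the wall thickness.

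**Check 1: no wall (D = L).** M2 = 0. M1 = 0.0416 × L^3:

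- L = 4.0 cm: 0.0416 × 64 = 2.7 g
- L = 5.0 cm: 0.0416 × 125 = 5.2 g
- L = 6.0 cm: 0.0416 × 216 = 9.0 g

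**Check 2: L = 5.0 cm, walls 1.0 cm (D = 7.0 cm).**

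- M1 = 0.832 × (1.05 × 343 − 125) = 0.832 × 235.15 = 195.6 g
- M2 = 0.8736 × (343 − 125) = 0.8736 × 218 = 190.4 g
- Excess 5.2 g, and 5.2 / 190.4 = 2.7%

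**Check 3: range over the assumed dimensions.**

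| LVID (cm) | Walls (cm) | As printed (g) | 1.05 on whole difference (g) | Excess |
|---|---|---|---|---|
| 4.0 | 1.2 | 175.8 | 173.1 | 2.7 g, 1.5% |
| 5.0 | 0.8 | 147.2 | 142.0 | 5.2 g, 3.7% |
| 5.0 | 1.0 | 195.6 | 190.4 | 5.2 g, 2.7% |
| 5.0 | 1.2 | 250.0 | 244.8 | 5.2 g, 2.1% |
| 6.0 | 0.8 | 203.8 | 194.8 | 9.0 g, 4.6% |

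The first and last rows are the smallest and largest relative excess over the grid examined.

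**Check 4: change score.** LVID goes from 5.0 to 5.2 cm with walls fixed at 1.0 cm.

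- As printed: +13.4 g
- 1.05 on the whole difference: +12.8 g
- Due to the bracket: 0.0416 × (5.2^3 − 5.0^3) = 0.0416 × (140.608 − 125) = 0.65 g, about 5% of the printed change (0.65 / 13.4)

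If LVID does not change, the excess is the same at both visits and drops out of the change.

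**The case against.** The strongest reply is that this is a slip in print. The section points to a cited source for the full echocardiographic protocol and names the analysis software, and neither is shown. The values may be computed correctly whatever the article prints. That stands as a limit: the fault shown is in the stated rule, not in any computed result. It does not excuse the text, because the formula is given explicitly, its brackets balance, and nothing else in the article corrects it.

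The second reply is that the effect is small. This also stands. The same rule would apply to both arms and all visits, so the group comparison is disturbed only through a difference between arms in cavity change. In the example that is well under 1 g. The wall-free ventricle proves the algebra but is not a possible participant.

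Three stronger readings are tempting, and the article does not support them:

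- **A density factor counted twice.** A reader may note that 0.832 = 0.8 × 1.04 and infer that 1.05 is a second density factor to be dropped. The article does not say what either constant contains, so this cannot be settled from it. Only the direction is safe: M1 exceeds 0.832 × (D^3 − L^3) as well, by 0.832 × 0.05 × D^3.
- **Cavity enlargement misread as muscle.** In the example most of the rise (+12.8 of +13.4 g) occurs with the bracket corrected too, because a larger shell of equal thickness has more volume.
- **The cardiac-structure results as a whole are compromised.** LVEDD, IVST and PWT are structural measures in their own right, and the formula does not touch them.

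**Conclusion.** The point holds as a minor error in the derivation rule of one secondary measure. As printed, the rule gives mass to a ventricle without walls and exceeds the version with 1.05 on the whole difference by 0.0416 × LVID^3. That is 2.7 to 9.0 g, or 1.5% to 4.6%, over the assumed dimensions. The sign of the excess and its independence from wall thickness follow from the algebra alone, while the gram and percentage figures rest on the assumed dimensions.

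LV mass and its index are affected if the printed rule is used. The primary endpoint (lean body mass by DXA) and the directly measured LVEDD, IVST and PWT are not. Which constants are correct remains open.

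**What to change.** Restate the rule as LV mass = constant × [(outer dimension)^3 − (cavity)^3], with both cubes inside one bracket. The outer dimension is the sum of cavity, septum and posterior wall. State that the cavity term is the end-diastolic diameter named in the same paragraph.

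Before LV mass is computed, reconcile 0.832 and 1.05 with the cited echocardiographic protocol and with what the analysis software applies, and write the resulting constant once. Use the same corrected formula for mass and index at baseline, 12 weeks and 32 weeks.

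The cost is a correction to the text and a check of one line of the derivation. The dimensions are measured and analysed off-line anyway, so no new measurement is needed and participants are not affected.
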